### Randomisation and allocation concealment

We randomise participants individually, stratified by country and sex, in blocks of variable size. An independent statistician developed the randomisation sequences uploaded into the Research Electronic Data Capture (REDCap) system. A researcher blinded to the sequence unveils group allocation through an autogenerated randomisation button on REDCap.

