**Methods and analysis:**

This prospective, randomised, two-arm, open-label, blinded-endpoint efficacy trial is being conducted in Montreal, Edmonton and Leicester. We are enrolling 100 persons 18–45 years of age within 6 years’ T2DM diagnosis, not on insulin therapy, and with obesity. During the intensive phase (12 weeks), active intervention participants adopt an 800–900 kcal/day low energy diet combining meal replacement products with some food, and receive supervised exercise training (aerobic and resistance), three times weekly. The maintenance phase (12 weeks) focuses on sustaining any weight loss and exercise practices achieved during the intensive phase; products and exercise supervision are tapered but reinstituted, as applicable, with weight regain and/or exercise reduction. The control arm receives standard care. The primary outcome is T2DM remission, (haemoglobin A1c of less than 6.5% at 24 weeks, without use of glucose-lowering medications during maintenance). Analysis of remission will be by intention to treat with stratified Fisher’s exact test statistics.

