### Sample size

In the DIRECT trial, remission was 46% at 1 year (vs 4% in control arm; OR 19.7).^9^ Even higher remission was observed over the shorter term in other studies.^57^ We initially allowed for a minimum 45% remission at 24 weeks in the intervention group and up to a 5% remission rate in the control group. Using a Fisher’s exact test with 90% power, a significance of 0.05, and a 1:1 ratio between intervention and control groups, we estimated needing 56 individuals to complete the trial (control=28, intervention n=28). Allowing for up to 30% drop-out, we planned to recruit 80 individuals in total (40 UK, 40 Canada) in our successful application for funding to the MRC and the Canadian Institutes of Health Research.

We subsequently obtained additional funding from the Canadian JR McConnell Foundation, and increased recruitment goals in Canada from 40 to 60 participants (40 UK, 60 Canada). With an overall sample size of 100 (40 UK, 60 Canada), if 70 (70%) complete the trial, we will have 90% power to detect a minimum 35% remission at 24 weeks in the intervention group and up to a 5% remission rate in the control group.

Retention of at least 35 participants in each arm (70 total) will provide over 80% power to detect a difference in mean peak early diastolic strain rate of 0.10/s difference, equivalent to the exercise effect in the DIASTOLIC trial (see BACKGROUND),^18^ assuming that the common SD is 0.144 as in the DIASTOLIC trial and using a two group t-test with a 5% two-sided significance level.

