### Statistical analyses

Our primary outcome measures the proportion of remission in the intervention arm relative to the control arm. We will apply intention-to-treat principles for the primary outcome, assuming that remission of diabetes did not occur if information is not available. Based on the DiRECT and DIADEM-I trials, we estimate that remission counts in the control arm could be less than 2. We will therefore use stratified Fisher’s exact test statistics (ie, stratification by country and by sex) if remission counts are low in the control arm but consider Pearson χ^2^ test, if appropriate. If numbers permit, logistic ORs with 95% CIs (exact method) will also be performed to further quantify the efficacy of intervention over the control group, after adjusting for factors used to stratify the randomisation (country, age or sex); we will not have missing values for these covariates. Subgroup analyses for the primary outcome will be performed by country, sex and the degree of weight loss (<5%, 5%–10%, 10%–15%, >15% as examined in the DiRECT trial,^9^ collapsing categories as needed, and by exercise adherence (<50%, >50% of supervised sessions attended). In a per-protocol analysis, we will restrict the intervention group to those who achieved at least 10% wt loss and adhered to at least two thirds of prescribed exercise sessions.

We will analyse dichotomous secondary outcomes (eg, diabetes remission at 12 weeks, hypertension remission at 12 and 24 weeks) as described for the primary outcome. We will analyse continuous key secondary outcomes (eg, left ventricular peak early diastolic strain rate, lean soft tissue mass) through linear regression or log-linear regression, as appropriate, with stratification by country and sex.

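### For continuous key secondary outcomes, a three-level site term would be a better adjustment factor than country, which merges Montreal and Edmonton; the gain is a modest amount of precision

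*Protocol article*

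**What the plan says.** The Abstract says that the trial "is being conducted in Montreal, Edmonton and Leicester", and the Setting section lists the same three centres. Allocation is described under Randomisation and allocation concealment: "We randomise participants individually, stratified by country and sex, in blocks of variable size". The Statistical analyses section carries the same two factors forward. For remission it plans "stratified Fisher’s exact test statistics (ie, stratification by country and by sex"), and for continuous key secondary outcomes it plans analysis "through linear regression or log-linear regression, as appropriate, with stratification by country and sex".

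The Sample size section gives the national split: "With an overall sample size of 100 (40 UK, 60 Canada), if 70 (70%) complete the trial". No split between Montreal and Edmonton is given. The same section states power for one continuous key secondary outcome, peak early diastolic strain rate: "Retention of at least 35 participants in each arm (70 total) will provide over 80% power" for "a difference in mean peak early diastolic strain rate of 0.10/s difference", "assuming that the common SD is 0.144 as in the DIASTOLIC trial", with a two-group t-test at the two-sided 5% level.

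On measurement, the article describes a 3-Tesla platform and cmr42 software, a core MRI protocol (Figure 2 legend), a named DXA model and one treadmill protocol. It does not describe the equipment of each site separately.

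**The concern.** Strain rate, VO2 peak and lean soft tissue mass are instrument-based measurements taken in three cities. A country term separates Leicester from Canada but treats Montreal and Edmonton as one place. If the two Canadian sites read systematically higher or lower than each other on a given outcome, that difference is left in the error term. A chance imbalance of the arms between the two sites then adds to the random error of the estimate.

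What is at stake is precision for secondary outcomes. It deserves a line because the stated power for strain rate clears 80% by less than two percentage points. Site is also known for every participant and determines country, so a site term keeps everything that the country term provides.

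This is a stated choice of adjustment factor, not a detail left to the statistical analysis plan.

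**Working it through.** **Inputs from the Sample size section.** 35 completers per arm (70 in total), difference 0.10/s, SD 0.144, two-sided 5%; planned recruitment of 40 in the UK and 60 in Canada.

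**Assumptions.** Completers follow the recruitment split: 70 × 0.40 = 28 in the UK and 70 × 0.60 = 42 in Canada. The 42 divide 21/21 between Montreal and Edmonton, with 30/12 as an alternative. The offset between the Canadian sites is additive and equals 0.25, 0.5 or 1 SD. There is no baseline adjustment.

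**Step 1: the plan's own figure.** The noncentrality is (0.10/0.144) × √(35/2) = 2.905 on 68 degrees of freedom. Power is 81.7%, which reproduces the stated figure of over 80%.

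**Step 2: residual SD with country only.** Let q be the share of Canadian completers at one of the two sites. The variance within Canada rises by q(1 − q) × offset². Averaged over all completers,

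residual variance = 0.144² + 0.60 × q(1 − q) × offset².

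With q = 0.5 this is 0.144² + 0.15 × offset². For an offset of 0.5 SD (0.072/s) it is 0.020736 + 0.15 × 0.005184 = 0.021514, so the SD is 0.147.

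**Step 3: power.**

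| Offset | Residual SD, 21/21 | Power, country only, 21/21 | Power, country only, 30/12 | Power with site |
|---|---|---|---|---|
| 0.25 SD (0.036/s) | 0.1447 | 81.3% | 81.4% | about 82% |
| 0.5 SD (0.072/s) | 0.1467 | 80.3% | 80.5% | about 82% |
| 1 SD (0.144/s) | 0.1544 | 76.1% | 77.1% | about 82% |

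With a 21/21 split, power falls below 80% once the offset exceeds about 0.079/s, or 0.55 SD.

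**Step 4: simulation check.** This used 4,000 trials per setting, permuted blocks within country and sex, and regression on arm, sex and either country or site. With country only, power was 80.2% at 0.5 SD and 76.4% at 1 SD; with site it was 81.3% and 81.4%. With no true effect, the country-only rejection rate lay between 4.5% and 5.4% over offsets of 0, 0.5 and 1 SD, so type I error holds.

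**Step 5: chance imbalance.** Assume 30 recruits at each Canadian site and 30 Canadians per arm. The number at one site allocated to intervention is hypergeometric with SD 1.95, and a split of 18:12 or worse occurs in 19.6% of trials. At 18:12 with a 0.5 SD offset the estimate moves by 0.072 × (18/30 − 12/30) × 0.60 = 0.009/s, about 9% of the 0.10/s target. The standard error of the treatment difference is 0.144 × √(2/35) = 0.034/s, so the shift is about a quarter of one standard error.

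**Step 6: with baseline.** If the baseline strain rate is in the model and the offset is the same at both visits, most of it is absorbed. At an assumed baseline-to-follow-up correlation of 0.5, simulated power with country against site was 89.7% against 90.1% for an offset of 0.10/s, and 88.6% against 90.0% for 0.20/s. At a correlation of 0.7 the gap was under 0.5 points.

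**The case against.** The strongest defence is that the plan analyses by the factors it randomises on, which is standard and internally consistent. Country is a reasonable stratum: recruitment targets, meal replacement products and care guidelines are all set by country. This stands. There is no contradiction in the article, and no reason to fault the randomisation.

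A reader might infer that the scanners, equipment or staff in Montreal and Edmonton are known to differ. The documents do not show this. The Setting section only names the centres, and the measurement sections describe common methods. The site-specific MRI practice in the article concerns optional sequences, not the cine images from which strain rate is derived.

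A reader might also infer that a chance site imbalance could pass for a treatment effect. Randomisation keeps the estimate unbiased over repeated trials, the unmodelled site variance is carried in the standard error, and simulated type I error stays near 5%. Only lost precision remains.

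Large losses of power need large offsets. An offset of 0.10/s is already 0.7 SD and equals the whole target difference, and 0.20/s is 1.4 SD. Baseline adjustment, which the statistical analysis plan may well specify, would remove most of the loss from an additive offset.

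Finally, a site main effect does not capture differences in how well the intervention is delivered at each site. Those act mainly in the intervention arm and are interactions, so they are no argument for this change.

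What survives is narrow. The article names the adjustment factor for these outcomes, and a finer factor that contains it is available at almost no cost.

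**Conclusion.** The point holds as a small, inexpensive gain in precision for continuous secondary outcomes. With country in the model, strain-rate power would fall from about 82% to 80.3% at a 0.5 SD offset and to about 76% at 1 SD. At 0.25 SD the loss is under half a point. The stated figure of over 80% survives any offset up to about 0.55 SD.

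These sizes rest on an assumed Montreal–Edmonton offset, an assumed 21/21 split of Canadian completers and no baseline adjustment. A less even split or a baseline term makes the loss smaller. The primary outcome, the allocation scheme and the validity of the tests are not in question.

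**What to change.** In the Statistical analyses section, for continuous secondary outcomes, replace country by site (Leicester, Montreal, Edmonton) and keep sex. Because site is nested in country, the model still respects the randomisation strata.

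The cost is one degree of freedom, which is negligible with 70 completers, and one line of wording to be settled before outcome data are seen. If the Canadian sites turn out not to differ, almost nothing is lost.

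Leave the randomisation lists unchanged. Leave the country-and-sex stratified exact test for remission unchanged too, because finer strata would be sparse with the few control-arm remissions expected.

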### Experimental group

#### Full meal replacement diet for 2 weeks

##### Dietitian review

Participants meet with the dietitian to discuss the first 2 weeks of the intervention which include only Optifast products (Nestlé), totalling 800–900 kcal/day (30% protein, 50% carbohydrate and 20% fat). To minimise constipation, participants are recommended to drink at least 2 L of calorie-free fluid each day, and receive a fibre-based laxative, to use as needed. They are offered a digital body weighing scale and asked to record weight weekly. They meet with the dietitian again in weeks 1 and 2 (virtually or in-person, as preferred).

##### Physician review

The study physician meets with the intervention arm participant to discuss antihyperglycaemic and antihypertensive medication withdrawal,^47^ given immediate lowering of glucose values and blood pressure with the dietary intervention. Glucagon-like peptide 1 receptors are stopped 1 week prior to the low energy diet. All other antihyperglycaemic medications are stopped the day that the diet is started. Except for ACE inhibitors or angiotensin receptor blockers prescribed for albuminuria (ie, RAAS blockade), participants stop antihypertensive medications on the day that the diet is initiated.

At weeks 1 and 2 follow-up (virtual or in-person), the physician reviews participant-recorded glucose and blood pressure data. Participants perform capillary blood glucose testing daily before breakfast and, on 1 day prior to physician follow-up, a 7-point glucose profile (measures before and 2 hours after food or meal replacement consumption and at bedtime). Antihyperglycaemic medications are not considered for reintroduction unless fasting morning capillary glucose is frequently 10 mmol/L or higher. Using the home blood pressure monitor provided, participants measure seated blood pressure each morning, after a 5 min rest period (second of two sequential measures). Antihypertensive agents are not be reintroduced unless systolic blood pressure values are generally 165 mm Hg or higher, as in the DiRECT trial.^48^ RAAS blockade may be interrupted with symptomatic hypotension.

Participants who may become pregnant are required to use reliable contraception. This is discussed, with referral as needed.

#### Partial meal replacement low energy diet and supervised exercise (weeks 3–12 inclusive)

##### Exercise physiologist

Starting at week 3, an exercise physiologist supervises 2 weekly sessions with aerobic and resistance components, at a designated facility. A third session is aerobic only, on site or elsewhere, as preferred, with self-monitoring (heart rate monitor and/or physical activity tracker provided). Participants increase exercise intensity and duration over time, with a goal of 60 min sessions.

Aerobic exercise on-site includes brisk treadmill walking (60%–80% of the maximum stress test heart rate). There is a high intensity interval walking option,^49^ to maximise improvements in fitness, insulin sensitivity^50^ and lean mass preservation.^51 52^ With walking challenges (eg, plantar fasciitis), cycle ergometer may be offered.

Resistance training with machines or free weights includes one to three sets of four upper body exercises (bench press, seated row, shoulder press and pull down), three leg exercises (leg press, extension, flexion) and exercises targeting stability, function and posture, with a goal of 8–12 repetitions per set. At 12 repetitions with good technique, the prescribed resistance is increased. Participants are instructed in resistance band use, in preparation for the maintenance phase.

##### Dietary component

Participants shift to partial meal replacement at week 3, with 800–900 kcal daily on non-exercise days and an additional 150–200 kcal from meal replacement products on exercise days. In addition to meal replacement products, the dietary ‘real food’ components are the equivalent of 125 mL of milk (or non-dairy alternative), careful attention to adequate protein intake from foods (meat, fish, egg or alternative), 1 portion of fruit and 2 portions of non-starchy vegetables each day. Because the variety of Optifast products are more limited in Canada than in the UK, ProtiDiet (soups, oatmeal and bars) are incorporated. Participants meet with the dietitian at weeks 4 and 8. The low energy diet is continued until week 12 and/or ideal weight (corresponding to body mass index of 25 kg/m^2^ for white participants and those of Indigenous origin and 23 kg/m^2^ in participants of non-white or mixed background.)

##### Physician review

Participants meet with the study physician at weeks 4 and 8. The systolic blood pressure threshold to consider antihypertensive reintroduction at this stage is 140 mm Hg, as in DiRECT.^48^

#### Maintenance phase of intervention

##### Dietary component

By week 12’s end, the dietitian and participant create an individualised plan for tapering meal replacement products, meeting again at weeks 14, 16, 18 and 21. The goal is to maintain any weight loss achieved in weeks 1–12. Meal replacement product tapering may be slowed, and product intake may even be increased again, in the event of weight regain.

##### Exercise component

Using monitoring tools, participants aim for 150 min of moderate to vigorous physical activity weekly, including three 30 min dedicated sessions at 60%–80% of the maximum heart rate. Participants may use the study exercise facility or engage in home-based or community-based exercise such as brisk walking and resistance training facilitated by bands. Participants have virtual or telephone contact with exercise physiologists at weeks 14, 16, 18 and 21. Those with less than 60 min of planned aerobic exercise and/or less than one resistance training session per week are asked to return for additional supervised sessions.

##### Physician monitoring

The study physician meets with participants at weeks 14 and 18. The thresholds for medication adjustment are as described previously. The HbA1c value at the intermediary evaluation may also be used to guide treatment.

##### End of intervention

Following final evaluations, intervention team members each meet with the participant to discuss strategies to maintain weight loss and exercise patterns. The study physician makes recommendations for medication management to the participant’s usual treating physician, in conformity with national diabetes management guidelines and the participant’s medication reimbursement plan regulations.

### Control group

The control group receives care from their usual physician, in accordance with National Institute for Health and Care Excellence^53^ and Diabetes Canada^54^ guidelines. Following final evaluations, control arm participants will be offered a 12-week low energy diet intervention followed by a 4-week food reintroduction period.

### Monitoring for adverse events

Intervention team members enquire about adverse events at each visit. Participants are asked to contact trial staff between visits to report any concerns. Serious adverse events will be reported within 7 days to all research ethics boards and the data monitoring committee, which may seek a formal adjudication of relatedness by physicians blinded to the treatment arm and who have not interacted with the study participants in question.

More common adverse events in low energy diet trials^9 55^ include constipation (18%–47%), headache (8%), dizziness (4%–32%), fatigue (11%–25%) and thirst (6%). Constipation responds to fibre-containing laxatives and fluid intake, and other symptoms resolve over time. In one high intensity aerobic training trial,^56^ 16% experienced fracture or lower extremity muscle cramping and/or muscle, ligament, or tendon strain; 5.2% experienced chest pain, difficulty breathing, dizziness or loss of consciousness. In a trial with a combined resistance and aerobic exercise arm,^19^ 12.5% had one of shoulder injury, left knee pain, spinal stenosis exacerbation or hip pain; one participant experienced atrial fibrillation.

### Withdrawal

Interventions and evaluations are halted in the event of intolerance to the study intervention or an adverse event that precludes participation, prolonged or serious hospital admission, the development of a serious comorbid condition such as active malignancy or pregnancy. We will document reasons for participant-initiated withdrawal, if specified.

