### Measurements

In-person evaluations occur before randomisation, at intervention period midpoint (12 weeks±1 week; no MRI study at this time point), and at intervention period end (24 weeks±2 weeks) (figure 1, table 1).

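### Halting evaluations together with the intervention on intolerance creates avoidable, treatment-related missing outcomes, chiefly for the week-24-only MRI measures

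*Protocol article*

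**What the plan says.** The Withdrawal section of the protocol article makes one decision out of two: "Interventions and evaluations are halted in the event of intolerance to the study intervention or an adverse event that precludes participation". It also lists a prolonged or serious hospital admission, and a serious new comorbid condition or pregnancy.

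The comparator is usual care: "The control group receives care from their usual physician" (Control group). Controls are offered a low energy diet only after their final evaluations.

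For remission, the Statistical analyses section states: "We will apply intention-to-treat principles for the primary outcome, assuming that remission of diabetes did not occur if information is not available". Dichotomous secondary outcomes follow the same approach. For continuous outcomes it says: "We will analyse continuous key secondary outcomes (eg, left ventricular peak early diastolic strain rate, lean soft tissue mass) through linear regression or log-linear regression", stratified by country and sex. It gives no missing-data rule for these.

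The Measurements section describes the intermediate evaluation as "at intervention period midpoint (12 weeks±1 week; no MRI study at this time point". Table 1 accordingly lists the MRI outcomes at week 24 only, while HbA1c, VO2 peak and DXA lean mass are listed at weeks 12 and 24.

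**The concern.** Stopping an intervention and stopping measurement are separate decisions, and an intention-to-treat comparison needs the second not to follow from the first. Here it does follow. Because controls receive no study intervention before their final evaluation, intolerance can end follow-up in one arm only, for a reason that treatment itself produces.

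This is a stated rule and not a gap left to an analysis plan. An analysis plan can say how to handle a missing week-24 scan or HbA1c, but it cannot recover one that was never taken.

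What is at stake differs by outcome:

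- **MRI outcomes.** With no week-12 scan, a participant halted before week 24 has only a baseline value. An analysis of observed data then compares those who tolerated the intervention with controls. Strain rate is the key secondary outcome named in the abstract and has its own power statement.
- **Primary outcome.** Nobody leaves the analysis, but an assumed value replaces one that could have been measured.
- **Planned subgroups.** The low weight-loss and low exercise-attendance categories need outcomes from people who did not manage the intervention well, and the rule stops evaluating some of them.

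**Working it through.** **1. The plan's own figures (Sample size section).**
- Strain rate: difference 0.10/s, SD 0.144, 35 per arm, two-sided 5% t-test. The noncentral t distribution gives power of 81.7%, so the stated figure of over 80% reproduces.
- Drop-out allowance in the initial plan: 56 / (1 − 0.30) = 80, which also reproduces. This 30% is all-cause loss over both arms, not an intolerance rate.

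**2. Strain rate, observed data only.** Let *m* be the share of the intervention arm halted for intolerance. Assume that stoppers gain nothing, that the others gain 0.10/s, that stoppers and non-stoppers would have the same mean without treatment, and that controls are fully observed.
- All-randomised effect = 0.10 × (1 − *m*)
- Observed-data effect = 0.10
- Overstatement = 0.10 × *m*

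| *m* (assumed) | All-randomised effect | Observed-data effect | Overstatement |
|---|---|---|---|
| 10% | 0.09/s | 0.10/s | 0.01/s (0.10/0.09: 11%) |
| 20% | 0.08/s | 0.10/s | 0.02/s (0.10/0.08: 25%) |
| 30% | 0.07/s | 0.10/s | 0.03/s (0.10/0.07: 43%) |

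Reduced numbers are the smaller problem. With 45, 40 or 35 intervention participants against 50 controls, power to detect 0.10/s is still 91.7%, 89.9% or 87.6%. The difficulty is that the 0.10/s being detected is no longer the effect in everyone randomised.

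**3. Primary outcome, missing counted as no remission.** Take 50 per arm and the planning rates of 35% and 5% if everyone were observed, with an unstratified two-sided Fisher's exact test. Assume that loss is unrelated to remission and occurs in the intervention arm only. The analysed intervention rate is 35% × (1 − *m*).

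| *m* (assumed) | Analysed rates | Difference | Power |
|---|---|---|---|
| 0% | 35.0% vs 5% | 30.0 points | 96.8% |
| 10% | 31.5% vs 5% | 26.5 points | 92.6% |
| 20% | 28.0% vs 5% | 23.0 points | 85.0% |
| 30% | 24.5% vs 5% | 19.5 points | 72.8% |

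For comparison, 30% loss in both arms gives 24.5% vs 3.5%, a difference of 21.0 points and power of 82.9%.

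If stoppers remit less often than others, the understatement is *m* × (remission rate among stoppers). At *m* = 20% with 10% to 30% of stoppers in remission, it is 2 to 6 points. If no stopper would have been in remission, it is zero.

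**The case against.** Much of the opposing case stands and limits the point.

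- **Intention to treat.** A reader might infer that the rule breaks the primary intention-to-treat analysis. It does not. Every randomised participant is kept, and the assumed non-remission works against the intervention. Remission also requires 12 weeks without glucose-lowering medication, so early stoppers who resume medication would be true non-remitters and the assumed value would be right for them.
- **One arm only.** A reader might infer that all withdrawal-related loss falls on the intervention arm. That is true of the intolerance trigger. Admission, comorbidity and pregnancy can arise in either arm.
- **Direction.** A reader might infer that all continuous outcomes are biased in favour of the intervention. The documents do not support this. The Discussion notes that low energy diets may reduce lean mass, so leaving out people who stopped the diet could bias that comparison the other way. Nor does intolerance show that a participant was doing worst on efficacy.
- **Exposure.** VO2 peak, lean mass and HbA1c have week-12 values, so someone halted after that visit still has post-baseline data.
- **Size.** The expected adverse events are described as manageable or transient, and no stopping rate is given. Reading the 30% drop-out allowance as intervention-arm intolerance would be an error.
- **Condensed text.** The analysis plan and full protocol are not shown. An observed-data analysis of strain rate is therefore an inference, and the qualifier about precluding participation may have been meant to cover intolerance as well as adverse events.

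The last point does not remove the concern. As written, the rule ends evaluations, and being unable to take part in the diet or exercise is not the same as being unable to attend for a blood test or a scan.

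**Conclusion.** The point holds in limited form. The rule produces missing outcomes that are avoidable and related to treatment, through a trigger that only the intervention arm can meet before week 24.

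The week-24-only MRI outcomes are the most exposed. For strain rate, an observed-data estimate could overstate the all-randomised effect by 0.01 to 0.03/s out of 0.10/s. That range is illustrative: it depends on assumed stopping shares of 10% to 30%, on zero benefit in stoppers, and on an observed-data analysis.

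For the primary outcome the effect is conservative. Under step 3's assumptions the difference falls from 30.0 points to between 26.5 and 19.5, and power from 96.8% to between 92.6% and 72.8%. There is no bias if no stopper would have remitted, but without measuring them nobody can tell. For other continuous outcomes neither direction nor size can be stated.

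**What to change.** Separate the two decisions in the Withdrawal section.

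- Leave the criteria for stopping the intervention unchanged; they are a clinical matter and are not judged here.
- State that participants who stop the intervention stay in the trial and are invited to the scheduled week 12 and week 24 evaluations, unless they withdraw consent or an assessment would be unsafe or uninterpretable.
- Set a minimum of week-24 HbA1c and medication history, with MRI where possible.
- In the Statistical analyses section, limit the assumption of no remission to data that cannot be obtained.

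The cost is a short amendment to the withdrawal text, consent wording if needed, and some effort to retain these participants for visits already in the schedule.
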